### Interventions

All eligible patients will be informed about the study and asked to give a written informed consent. They will receive standard information about stroke concerning the pathophysiology and risk factors according to established clinical praxis during their hospitalization. They will also be offered a follow-up visit to a stroke nurse and an outpatient follow-up according to normal care procedures.

Patients randomized to the intervention group will be contacted by a study nurse by phone one month after discharge. Before the call, a blood sample for lipids will be taken and a standardized blood pressure control will be performed. Blood pressure will be measured after five minutes in the sitting position and after one minute standing. The tests will be performed by a district nurse, or, for patients in the intervention group living close to the hospital, by a study nurse. Self-reported compliance with medication will be recorded. During the call the patient will be informed about the test results and whether a change in medication is necessary. Tobacco use, physical activity and dietary habits will be discussed. Smoking cessation will be encouraged and supported. Physical activity of moderate intensity for 30 minutes or more, most days of the week will be encouraged, but also adjusted to the individual patient’s capacity. Dietary advice to reduce saturated fat and increase the intake of fruit and vegetables will be given. If the patient’s cholesterol or blood pressure values are higher than anticipated, medication will be adjusted after contact from a study physician. Repeated tests will be taken within approximately four weeks and further adjustments made if necessary until target values are reached or no further changes can be considered realistic. The same routine, with an Hb1C test added, will be applied after 12, 24 and 36 months.

The target values are: blood pressure <140/<90 mmHg (optionally <130/<80 mmHg in patients at very high risk, that is, diabetic subjects), total cholesterol <4.5 mmol/l, LDL <2.5 mmol/l [13,14].

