Patients randomized to the usual care group will also be contacted by phone one month following discharge after blood pressure and lipid profile have been checked. Self-reported compliance, tobacco use and physical activity will be recorded. All medical care will be given by their treating physician, usually a general practitioner, who will receive the test results (lipid profile and blood pressure), and no additional intervention will be given as a result of participation in the study. The same routine, with an Hb1C test added, will be applied after 12, 24 and 36 months, Figure 1.

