### Outcomes

Outcomes will be measured after 12, 24 and 36 months of follow-up. Outcome variables are sitting systolic and diastolic blood pressure, LDL cholesterol and total cholesterol, as well as the proportion of patients achieving the set target for these variables. Standing systolic and diastolic blood pressure, smoking rates, the proportion of patients treated with different secondary preventive drugs, diabetes control by Hb1C, change in body mass index (BMI) and physical activity will also be measured. Sitting systolic blood pressure at 36 months will be analyzed as the primary outcome. The analyses of the secondary outcomes will be exploratory.

Blood pressures measurements are standardized as described above. LDL values are calculated from the serum concentrations of cholesterol and fasting triglycerides using the Friedewald formula. Smoking (yes/no) and physical activity (duration/week) are self-reported. Deaths are available in the hospital records and will be recorded in order to detect any survival difference between groups.

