### Sample size

To reliably detect a difference between groups in mean systolic blood pressure of 5 mmHg requires study groups of 180 participants (standard deviation 19, mean systolic blood pressure 140 versus 135, alpha 0.05 two-tailed, power 80%). Study groups of at least 200 participants are planned to allow for drop-outs. This sample size is also adequate for detection of clinically meaningful group differences in lipid values (0.3 mmol/l, standard deviation 1.0), smoking rates (10%), proportion reaching treatment goals (10%), change in BMI (1.0, standard deviation 4.0) and change in physical activity (10%, proportion in a given activity level), calculated with two-tailed alpha 0.05, power 80%.

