### Statistical methods

The primary analysis will be performed according to the intention-to-treat principle using a linear regression model adjusting for gender and degree of disability. The adjustment is made in order to reflect the stratified randomization process. Per protocol analyses will also be performed. Secondary outcomes will be analyzed using the primary analysis model when continuous, and using a logistic regression model, adjusting for the same covariates, when outcomes are binary. In order to assess whether there are indications of differential treatment effects across subgroups (age, gender, co-morbidity, level of education and social classification), tests for interaction will be performed, although this aim is secondary because the study is not powered for this particular purpose. Adjustment for relevant baseline covariates will be performed in additional exploratory analyses of primary and secondary outcomes in order to evaluate the effect of possible baseline imbalance. All tests will be two-sided and a *P*-value of <0.05 will be considered significant.

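### The main smoking model leaves out smoking status at entry, which gives away power that a one-line change in wording would largely recover

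*Protocol article*

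**What the plan says.** All references are to the protocol article.

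- **Outcomes:** "Smoking (yes/no) and physical activity (duration/week) are self-reported". Smoking rates are among the further outcomes measured at 12, 24 and 36 months. Systolic pressure at 36 months is the single primary outcome, and secondary analyses are declared exploratory.
- **Statistical methods:** binary secondary outcomes are analysed "using a logistic regression model, adjusting for the same covariates, when outcomes are binary", meaning gender and disability. The same section adds exploratory analyses adjusted for baseline covariates judged relevant. These are not named, and their purpose is to examine imbalance.
- **Interventions:** in the intervention group, "Smoking cessation will be encouraged and supported". In the usual care group, at the one-month call, "Self-reported compliance, tobacco use and physical activity will be recorded".
- **Sample size:** "Study groups of at least 200 participants are planned to allow for drop-outs". This size is called adequate for a 10-point difference in smoking rates at two-sided 5% and 80% power. No control rate is given.
- **Participants and Randomization:** entry does not depend on smoking, and the strata are gender and modified Rankin score only.

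**The concern.** The denominator is every randomized patient, while the component meant to change smoking works mainly through those who smoke. Status at entry is likely to be by far the strongest predictor of status at follow-up. Leaving it out of the main model means that any chance difference between arms in the number of starting smokers passes almost undiluted into the comparison.

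The article treats its other lifestyle measures differently. The Sample size section words BMI and physical activity as change, so starting values count there. Smoking is a raw follow-up rate.

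The abstract names tobacco use as one of four focus areas. A null result from an underpowered model would say little about it.

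**Working it through.** **Inputs from the article:** 1:1 allocation; at least 200 per group, with 180 the number required for the primary outcome; two-sided alpha 0.05; a 10-point difference in smoking rate.

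**Assumed, because the article is silent:** share of smokers at entry *b* = 15%, 20% or 30%; quit rates 20% vs 45%, or 30% vs 50%; 2% of non-smokers smoking later; 180 analysed per arm.

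**1. The stated sample size.** With a pooled-variance test, n = [1.96·√(2p̄(1−p̄)) + 0.8416·√(p₁(1−p₁)+p₂(1−p₂))]² / d². For an assumed 20% vs 10%: [1.96·√0.255 + 0.8416·√0.25]² / 0.01 = (0.990 + 0.421)² / 0.01 ≈ 199 per group. Power at 200 is 80.2%, and at 180 it is 75.9%. Other control rates change this: at 200 per group, 15% vs 5% gives 91.8%, 25% vs 15% gives 70.7% and 30% vs 20% gives 63.8%. The adequacy statement is reproducible for a control rate of about 20% or lower.

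**2. What 10 points means among smokers.** Ignoring uptake, the needed difference in quit rates is 0.10/*b*: 0.10/0.15 = 67 points, 0.10/0.20 = 50 points, 0.10/0.30 = 33 points.

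**3. Chance imbalance at entry.** With *b* = 20% and 180 per arm, the between-arm difference in starting smokers has standard deviation √(2·0.20·0.80/180) = 4.2 points. A quit-rate difference of 20–25 points moves the all-patient rate by 0.20·20 to 0.20·25 = 4–5 points. Noise from entry status is as large as the effect.

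**4. Power with and without entry status.** Simulated logistic models with treatment, gender and disability, all randomized patients:

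| Quit rates | Smokers at entry | Planned model | Plus entry status | Relative loss |
|---|---|---|---|---|
| 20% vs 45% | 15% | 18% | 33% | 1−18/33 = 45% |
| 20% vs 45% | 20% | 24% | 46% | 1−24/46 = 48% |
| 20% vs 45% | 30% | 40% | 72% | 1−40/72 = 44% |
| 30% vs 50% | 15% | 14% | 24% | 1−14/24 = 42% |
| 30% vs 50% | 20% | 20% | 32% | 1−20/32 = 38% |
| 30% vs 50% | 30% | 30% | 53% | 1−30/53 = 43% |

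Repeat simulations agreed to within 4 points. With equal quit rates, each model rejects about 4–6% of the time.

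**5. Closed-form check of direction.** This uses 200 per arm and no uptake, and compares all patients with entry smokers only: power = Φ{[d√n − 1.96√(2p̄(1−p̄))]/√(p₁(1−p₁)+p₂(1−p₂))}. For *b* = 20% and quit rates 30% vs 50%:
- All patients, 14% vs 10%: Φ[(0.566−0.901)/0.459] = 23%.
- The 40 smokers per arm, 70% vs 50%: Φ[(1.265−1.358)/0.678] = 45%.

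The all-patient comparison was weaker at every *b* tried from 10% to 40%, except where both were near 100%.

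**6. At the protocol's own 10-point effect.** Control rates of 15–25% with *b* = 20–35% give all-patient power of 71–92% against 94–100% among smokers. The relative loss runs from 1−0.918/0.970 = 5% to 1−0.707/1.000 = 29%. Smokers-only power exceeded status-adjusted power in every simulated setting (48% vs 33%, 62% vs 48% and 79% vs 72% for 20% vs 45%), so the loss against the status-adjusted model should be no larger.

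**The case against.** Much can be said for the plan, and most of it stands.

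- **Smoking is exploratory.** No confirmatory claim rests on it. This stands and limits the weight of the point.
- **Adjustment is already foreseen.** The additional exploratory analyses could include smoking at entry, and an article need not list covariates for each outcome. This stands in part: the article does fix the main model for binary outcomes, and entry smoking is not in it.
- **The all-patient rate is a legitimate target.** It respects intention-to-treat, suits a population-based trial and captures relapse among patients who have already stopped. This stands. It argues against replacing the all-patient analysis with one in smokers, but not against a covariate.
- **Smokers-only power is still limited.** With 0.15·180 = 27 to 0.30·180 = 54 smokers per arm, power is 48–79% even for 20% vs 45%. This stands.

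A reader might infer that the one-month call supplies a clean starting status. The documents do not support that. Patients are randomized soon after the event, so the call comes after randomization, and in the intervention group it is also the contact at which cessation support is given. Only status at admission is free of this, and the article does not say how that is recorded.

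**Conclusion.** The point holds as an improvement in efficiency. Under the assumed values, the planned model has about 14–40% power and the model with entry status about 24–72%, a relative loss of 38–48%. These figures depend on prevalences, quit rates and uptake that the documents do not give.

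Four stronger readings are tempting but unsupported:
- **More than half the power is lost.** Against the status-adjusted model the loss stays below half in all six settings. Against a smokers-only analysis it passes half only in some, and at the protocol's own 10-point effect it is 5–29%.
- **Most patients cannot respond.** This presumes a smoking prevalence below one half, which is plausible but not stated, and it ignores relapse.
- **The sample size statement on smoking is wrong.** It reproduces at 20% vs 10%. It lacks a control rate.
- **The planned test is invalid.** Its type I error is sound; only precision suffers.

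Because smoking is a secondary, exploratory outcome, this is minor.

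**What to change.** In Statistical methods, state that the main logistic model for smoking at 12, 24 and 36 months includes treatment, gender, disability and smoking status at admission, before randomization, in all randomized patients. Prespecify as supporting analysis the proportion not smoking at each visit among patients who smoked at admission, with the same model less that covariate. Use the one-month answer only if admission status was not recorded, and then say that it was obtained after randomization. Leave the outcome labelled exploratory.

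The cost is wording, plus a check that admission status is on record for every patient. The odds ratio becomes conditional on starting status and is not interchangeable with the planned one, so smoking rates by arm should be shown beside it. The supporting estimate will have a wide interval because few patients contribute.

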## Discussion

Stroke is one of the major diseases in the current ageing population, with substantial consequences for individuals and society. The knowledge of secondary preventive measures to prevent further disease in stroke patients is strikingly low. Further research in the areas of compliance, the possibility of participation in secondary preventive studies and the possibility of reaching treatment goals in a cohort of stroke patients representative for clinical praxis is absolutely necessary.

This study covers all patients in one Swedish county, who after TIA or stroke, will be eligible for inclusion, thus avoiding selection bias. This allows us to study even very old and very sick stroke patients, who are usually not included in randomized stroke studies. Their ability to participate in secondary prevention programs and their tolerability of medication when attempting to achieve set treatment goals are of great interest as these have significant consequences for health economics and mortality and morbidity rates.

The study design has several other advantages. Randomization of the patients soon after the stroke or TIA allows us to study the acute phase as well as to perform a long-term follow-up. By establishing an early contact, no patient is expected to be lost to follow-up. The immediate recruitment and the logistics to include each and every stroke and TIA patient will show the true proportion of possible participants in the secondary preventive program.

As it is well known that information and team rehabilitation after stroke affects the outcome, the study is designed so that each eligible patient will receive the same present standard of care regardless of randomization group.

Our intention is to combine a nurse-led life-style intervention with a rapid pharmaceutical titration model aiming to achieve set treatment goals of the most important risk factors after stroke. The long-term follow-up and the relatively large number of patients involved will provide important new data in the field of improving secondary prevention after stroke. Cost-effectiveness of this method of handling stroke follow-up can be studied, and we are of the opinion that this method - if proven effective - could be implemented in general clinical practice at a low cost. The study logistics are deliberately made as simple as possible in order to be generalizable to the Swedish as well as to other national health care systems. Although the study is performed in a single county, the information on better control of standard risk factors is also likely to be valid in other health care systems.

## Trial status

Ongoing.

## Abbreviations

TIA: Transient ischemic attack; BMI: Body mass index; LDL: Low-density lipoprotein.
